***Derivation of variables***

Age will be defined by the age that the patient was on the date of their operative procedure. The number of patients undergoing surgery will be categorised into 5-year age epochs e.g. Age 0-4, 5-9, 10-14…. until 90+. The lifetime risk will be calculated and repeated for consecutive years that we have data available, this has been done in previous papers assessing the lifetime risk of diabetes(9, 10).

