***Impact of COVID-19 Pandemic***

We will consider COVID-19 as an exposure and calculate its impact on the lifetime risk of having surgery. The impact of the COVID-19 pandemic on the lifetime risk of surgery will be investigated by assessing for any difference in lifetime risk in the specified time-period for pre-pandemic and pandemic. We will do this by generating the five-year epochs for the pre-pandemic period and then for the pandemic period and comparing the two. To investigate for a significant statistical difference between the lifetime risk of surgery in the pre-pandemic period and the pandemic period we will use two methods. The first test will involve using 95% confidence intervals(12). If the 95% confidence intervals for the lifetime risk of surgery in the pre-pandemic period does not overlap with the 95% confidence intervals in the pandemic period or the 95% uncertainty interval for relative percentage change does not include 0 then there will be a statistically significant difference in the lifetime risk of surgery between the pre-pandemic and pandemic periods(12). The second test will be a T-test, a P-value 0.05 will be considered statistically significant.

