**Appendix 2**

### *The Life Table Method*

We calculated lifetime risk for both men and women in a sex-differentiated fashion because the life table method does not allow combined analyses. The incident rate of surgery in person-years was calculated for each 5-year epoch. We calculated surgical mortality rate and the all-cause mortality rate in person-years for each 5-year epoch.

The probability of no longer being alive and surgery free was calculated using equation 1^4^:

$$\lambda_{i}=r_{i}+m_{i}-s_{i}$$

Where $r_{i}$ is the incident rate of surgery in person years, $m_{i}$ is the all-cause mortality rate and $s_{i}$ is the surgical mortality rate. The probability of being alive and without previous surgery at age i was calculated using equation 2^4^:

$$S_{0}(i)=exp[-5\sum_{x=5}^{i} \lambda_{i}]$$

This was multiplied by 5 due to 5-year epochs being used.

Lifetime risk at age *i* was then calculated using equation 3^4^:

$${l_{i}=S}_{0}(i)\times r_{i} \times\frac{1-exp(-{5(\lambda}_{i}))}{\lambda_{i}}$$

The lifetime risk for period *y* (e.g. from 0-90) is calculated using equation 4^4^:

$$LR(y)= \sum_{i=0}^{90} l_{i}(y)$$

*Cumulative Lifetime Incidence*

Cumulative incidence was also used to estimate the lifetime risk of surgery, it was possible to calculate the overall cumulative lifetime incidence of first and all surgery as this method does not rely on mortality rates so male and female data can be combined. We calculated this using equation 6^10^:

$$P=1-exp(-5\sum_{x=5}^{i} r_{i})$$

Where P was the cumulative incidence until age i and $r_{i}$ is the incidence rate in person-years. This was multiplied by 5 as we used 5-year epochs.

**Supplementary figure 1:** Men (blue line) compared to women (red line) cumulative lifetime incidence of first surgery based on the years 2016-19. Error bars are the 95% CIs.

**Supplementary figure 2:** Men (blue line) compared to women (red line) cumulative lifetime incidence of all surgery based on the years 2016-19. Error bars are the 95% CIs.

**Supplementary figure 3:** Pre-pandemic (blue line) compared to the pandemic (red line) lifetime risk of all surgery for men and women (Error bars are 95% CIs). The pre-pandemic period was based on data from 2016-19 and the pandemic period was based on data from 2020. This was calculated using the life table method.

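### The pandemic comparison adds a T-test with no defined observations to an interval test that already holds 5%, and no rule says which one decides

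*SAP*

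**What the plan says.** The SAP's one secondary objective is the impact of the pandemic on the lifetime risk of surgery. For the comparison between the "pre-pandemic period and the pandemic period we will use two methods".

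- **First method.** Significance is declared if one period's 95% confidence interval "does not overlap with the 95% confidence intervals in the pandemic period". It is also declared, as an alternative, when "the 95% uncertainty interval for relative percentage change does not include 0". Either condition is enough.
- **Second method.** "The second test will be a T-test, a P-value 0.05 will be considered statistically significant".

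The material to be compared is described as "generating the five-year epochs for the pre-pandemic period and then for the pandemic period and comparing the two". In Appendix 2, lifetime risk is calculated separately for men and women, and "The lifetime risk for period *y* (e.g. from 0-90) is calculated using equation 4", which is a sum over the age bands. Derivation of variables adds that "The lifetime risk will be calculated and repeated for consecutive years that we have data available", but does not link those yearly values to either method. The change log of 22 December 2023 replaces the life-table equations and leaves the tests as they were.

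**The concern.** A t-test needs replicate observations and a variance estimated from them. The SAP names the test without saying what its observations are, whether they are paired, or where the variance comes from. The quantity compared is one number per period and sex, so the unit has to be supplied by whoever runs the analysis, possibly after seeing the data. The candidate units do not give similar answers.

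The SAP also names no deciding method and has no rule for a disagreement. A conclusion on the secondary objective could then rest on an unstated choice of unit, or on whichever of two methods gave the preferred result.

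**Working it through.** The SAP gives no sample size, power or computed figure for this comparison, so there is none to reproduce. The check is how each rule behaves against the stated 0.05.

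**Inputs from the SAP**
- Two methods, with a threshold of 0.05 for the T-test.
- 19 age bands, 0-4 to 90+ (Derivation of variables; sample table 3).
- Pre-pandemic data from 2016-19 and pandemic data from 2020 (figure captions in Appendix 2), so four years against one.

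**Assumed, because the SAP gives no values**
- Remaining lifetime risk falling linearly over the 19 bands, from 60% to 10% or from 60% to 30%.
- Standard errors of 0.1 and 0.2 percentage points for the overall lifetime risk (60%) in the two periods.
- The same proportional fall in every band.

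**1. First method.** Let d be the difference and s1, s2 the two standard errors.
- Non-overlap needs |d| > 1.96(s1 + s2).
- An interval for the change that excludes 0 needs |d| > 1.96 sqrt(s1² + s2²).
- Since (s1 + s2)² = s1² + s2² + 2·s1·s2, the first threshold is never below the second. Non-overlap therefore adds no rejections.
- In 2,000,000 simulated pairs per setting, on the difference and relative-change scales and with standard-error ratios of 1 and 2, non-overlap never occurred without the interval also excluding 0. The error of the combined rule was 0.0499 to 0.0501.

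**2. T-test on one value per period.** The degrees of freedom are 1 + 1 − 2 = 0, so p is undefined.

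**3. T-test across the 19 age bands.** The unpaired variance is the spread of risk across ages, not sampling error. In the paired test each difference is r times the pre-pandemic value, where r is the proportional fall. The factor r cancels from the t statistic, so p is the same for any uniform fall, however small.

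| Uniform fall | Unpaired p (60→10) | Unpaired p (60→30) | Paired p (60→10; 60→30) | z for overall lifetime risk |
| --- | --- | --- | --- | --- |
| 0.5% | 0.97 | 0.94 | 1.3e-8; 4.4e-14 | 1.34 |
| 10% | 0.47 | 0.13 | same | 26.8 |
| 20% | 0.14 | 0.002 | same | 53.7 |
| 30% | 0.022 | below 0.001 | same | 80.5 |

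The last column is 60r / sqrt(0.1² + 0.2²). For a 20% fall this is 12 / 0.2236 = 53.7; for 0.5% it is 0.3 / 0.2236 = 1.34.

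**4. T-test on yearly values, four against one.** Welch's test needs a variance from each group, and one value gives none, so it is undefined. The pooled test has 4 + 1 − 2 = 3 degrees of freedom and takes all its variance from the pre-pandemic years. It needs a gap of t(0.975; 3) × sqrt(1 + 1/4) = 3.182 × 1.118 = 3.56 between-year SDs.

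**5. Either method sufficing.** If each held 5%, the chance of at least one false positive is 1 − 0.95² = 0.0975 under independence, and at most 0.05 + 0.05 = 0.10 under any dependence.

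**The case against.** The strongest reply is that the sample is undefined rather than impossible. Yearly lifetime risks are already planned, and T-test may be loose wording for an estimate divided by its standard error. Both are fair. A reader might infer that no valid sample could exist; the SAP does not support that. But it does not tie the yearly values to the test, and an estimate-over-standard-error statistic would largely duplicate the interval in the first method. The gap therefore stands on either reading.

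Three other strong readings are tempting and should not be made.

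- **That the first method is an overlap rule and so not a 5% test.** Taken alone, non-overlap would have an error of 0.0056 with equal standard errors and 0.0085 with a 1:2 ratio. The SAP does not use it alone. The alternative condition, "the 95% uncertainty interval for relative percentage change does not include 0", brings the whole rule to 5%.
- **That the intervals will call ordinary yearly drift a pandemic effect.** This assumes intervals that reflect counting error only. The SAP promises 95% intervals without stating a variance method, so the size of any such effect cannot be derived from it. That a before-after comparison cannot isolate the pandemic is a limit of the design, not a fault in these tests.
- **That the 2020 value should instead be judged against a prediction interval from 2016-19.** Its half-width is t(0.975; 3) × sqrt(1.25) = 3.56 SDs, so it is the pooled four-against-one t-test under another name. It would also set 2020, for which data end on 31 August, against full years.

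**Conclusion.** The defect is confined to the T-test and the missing decision rule. The T-test is undefined on one value per period and can err in either direction across age bands. On yearly values it is either undefined (Welch) or left with 3 degrees of freedom (pooled). It can therefore contradict the first method: under the 60→10 profile, a 20% fall gives unpaired p = 0.14 while the overall estimate has z of about 54, and a 0.5% fall gives paired p of about 1e-8 while the overall z is 1.34.

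These p-values depend on the assumed profiles, standard errors and uniform fall. They show the direction of the problem, not its size in the real data. The results that need no assumed risk values are the 0 degrees of freedom, the undefined Welch test, the 3.56 SD requirement and the redundancy of the overlap clause on the difference scale. The 9.75% to 10% figure applies only if either method may decide and each holds 5%, which is not established for the T-test. The 5% error of the first method assumes a correctly derived variance.

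This should be fixed. It is not critical, because it concerns the secondary objective and a usable test is already in the SAP.

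**What to change.** In Impact of COVID-19 Pandemic:

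- Delete the T-test and the overlap clause.
- Make the 95% interval for the relative change (or the difference) in lifetime risk, by sex, the single deciding analysis.
- State how the variance is obtained: carried through from the age-specific rates by the delta method or a bootstrap, resampling patients where repeat operations count.
- Optionally, show the yearly lifetime risks already planned, as description only and over comparable calendar windows because data end on 31 August 2020, so that readers can judge ordinary drift.

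The cost is a few lines of SAP wording and a little analysis work. The planned T-test is lost, but it has no defined result to lose.

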***Research Ethics approval***

This analysis of routinely collected, pseudonymised data was approved by the Health Research Authority (20/HRA/3121). Access to NHS England data was approved by the NHS Digital Independent Group Advising on the Release of Data (DARS-NIC-375669-J7M7F).

***Handling of missing data***

Patients missing data will be excluded from the analysis.

**SAP: Sample tables and flow chart**

**Sample table 1: Life Tables**

| **Age (years)** | Population | Incident rate of surgery | Mortality rate for those undergone surgery | Mortality rate for those who have not undergone surgery | Probability of transition from no surgery to surgery | Probability of transition from no surgery to death | Probability of transition from surgery to death | Proportion of hypothetical cohort undergoing surgery |
| --- | --- | --- | --- | --- | --- | --- | --- | --- |
| **0-4** |  |  |  |  |  |  |  |  |
| **5-9** |  |  |  |  |  |  |  |  |
| **10-14** |  |  |  |  |  |  |  |  |
| **15-19** |  |  |  |  |  |  |  |  |
| **20-24** |  |  |  |  |  |  |  |  |
| **25-29** |  |  |  |  |  |  |  |  |
| **30-34** |  |  |  |  |  |  |  |  |
| **35-39** |  |  |  |  |  |  |  |  |
| **40-44** |  |  |  |  |  |  |  |  |
| **45-49** |  |  |  |  |  |  |  |  |
| **50-54** |  |  |  |  |  |  |  |  |
| **55-59** |  |  |  |  |  |  |  |  |
| **60-64** |  |  |  |  |  |  |  |  |
| **65-69** |  |  |  |  |  |  |  |  |
| **70-74** |  |  |  |  |  |  |  |  |
| **75-79** |  |  |  |  |  |  |  |  |
| **80-84** |  |  |  |  |  |  |  |  |
| **85-89** |  |  |  |  |  |  |  |  |
| **90+** |  |  |  |  |  |  |  |  |

**Sample table 2: Incident rate**

|  | **__ to __** | | **__ to __** | |
| --- | --- | --- | --- | --- |
| **Age groups (years)** | **Number of patients undergoing surgery** | **Person-years lived** | **Number of patients undergoing surgery** | **Person-years lived** |
| **0-4** |  |  |  |  |
| **5-9** |  |  |  |  |
| **10-14** |  |  |  |  |
| **15-19** |  |  |  |  |
| **20-24** |  |  |  |  |
| **25-29** |  |  |  |  |
| **30-34** |  |  |  |  |
| **35-39** |  |  |  |  |
| **40-44** |  |  |  |  |
| **45-49** |  |  |  |  |
| **50-54** |  |  |  |  |
| **55-59** |  |  |  |  |
| **60-64** |  |  |  |  |
| **65-69** |  |  |  |  |
| **70-74** |  |  |  |  |
| **75-79** |  |  |  |  |
| **80-84** |  |  |  |  |
| **85-89** |  |  |  |  |
| **90+** |  |  |  |  |

**Sample table 3: Lifetime Risk**

|  | **Pre-Pandemic** | | **Pandemic** | |
| --- | --- | --- | --- | --- |
| **Age groups (years)** | **Lifetime risk (%)** | **95% CI** | **Lifetime risk (%)** | **95% CI** |
| **0-4** |  |  |  |  |
| **5-9** |  |  |  |  |
| **10-14** |  |  |  |  |
| **15-19** |  |  |  |  |
| **20-24** |  |  |  |  |
| **25-29** |  |  |  |  |
| **30-34** |  |  |  |  |
| **35-39** |  |  |  |  |
| **40-44** |  |  |  |  |
| **45-49** |  |  |  |  |
| **50-54** |  |  |  |  |
| **55-59** |  |  |  |  |
| **60-64** |  |  |  |  |
| **65-69** |  |  |  |  |
| **70-74** |  |  |  |  |
| **75-79** |  |  |  |  |
| **80-84** |  |  |  |  |
| **85-89** |  |  |  |  |
| **90+** |  |  |  |  |

**Sample Flow chart**

**
[figure not shown]
**

**Change log for SAP:**

22^nd^ December 2023

We have made the following changes for the life table method to acknowledge a new interpretation and the methods were amended to this.

We calculated lifetime risk for both men and women in a sex-differentiated fashion because the life table method does not allow combined analyses. The incident rate of surgery in person-years was calculated for each 5-year epoch. We calculated surgical mortality rate and the all-cause mortality rate in person-years for each 5-year epoch.

The probability of no longer being alive and surgery free was calculated using equation 1^4^:

$$\lambda_{i}=r_{i}+m_{i}-s_{i}$$

Where $r_{i}$ is the incident rate of surgery in person years, $m_{i}$ is the all-cause mortality rate and $s_{i}$ is the surgical mortality rate. The probability of being alive and without previous surgery at age i was calculated using equation 2^4^:

$$S_{0}(i)=exp[-5\sum_{x=5}^{i} \lambda_{i}]$$

This was multiplied by 5 due to 5-year epochs being used.

Lifetime risk at age *i* was then calculated using equation 3^4^:

$${l_{i}=S}_{0}(i)\times r_{i} \times\frac{1-exp(-{5(\lambda}_{i}))}{\lambda_{i}}$$

The lifetime risk for period *y* (e.g. from 0-90) is calculated using equation 4^4^:

$$LR(y)= \sum_{i=0}^{90} l_{i}(y)$$

**Appendix 2**

### *The Life Table Method*

We calculated lifetime risk for both men and women in a sex-differentiated fashion because the life table method does not allow combined analyses. The incident rate of surgery in person-years was calculated for each 5-year epoch. We calculated surgical mortality rate and the all-cause mortality rate in person-years for each 5-year epoch.

The probability of no longer being alive and surgery free was calculated using equation 1^4^:

$$\lambda_{i}=r_{i}+m_{i}-s_{i}$$

Where $r_{i}$ is the incident rate of surgery in person years, $m_{i}$ is the all-cause mortality rate and $s_{i}$ is the surgical mortality rate. The probability of being alive and without previous surgery at age i was calculated using equation 2^4^:

$$S_{0}(i)=exp[-5\sum_{x=5}^{i} \lambda_{i}]$$

This was multiplied by 5 due to 5-year epochs being used.

Lifetime risk at age *i* was then calculated using equation 3^4^:

$${l_{i}=S}_{0}(i)\times r_{i} \times\frac{1-exp(-{5(\lambda}_{i}))}{\lambda_{i}}$$

The lifetime risk for period *y* (e.g. from 0-90) is calculated using equation 4^4^:

$$LR(y)= \sum_{i=0}^{90} l_{i}(y)$$

*Cumulative Lifetime Incidence*

Cumulative incidence was also used to estimate the lifetime risk of surgery, it was possible to calculate the overall cumulative lifetime incidence of first and all surgery as this method does not rely on mortality rates so male and female data can be combined. We calculated this using equation 6^10^:

$$P=1-exp(-5\sum_{x=5}^{i} r_{i})$$

Where P was the cumulative incidence until age i and $r_{i}$ is the incidence rate in person-years. This was multiplied by 5 as we used 5-year epochs.

**Supplementary figure 1:** Men (blue line) compared to women (red line) cumulative lifetime incidence of first surgery based on the years 2016-19. Error bars are the 95% CIs.

**Supplementary figure 2:** Men (blue line) compared to women (red line) cumulative lifetime incidence of all surgery based on the years 2016-19. Error bars are the 95% CIs.

**Supplementary figure 3:** Pre-pandemic (blue line) compared to the pandemic (red line) lifetime risk of all surgery for men and women (Error bars are 95% CIs). The pre-pandemic period was based on data from 2016-19 and the pandemic period was based on data from 2020. This was calculated using the life table method.

**Supplementary figure 4:** Pre-pandemic (blue line) compared to the pandemic (red line) lifetime risk of first surgery for men and women (Error bars are 95% CIs). The pre-pandemic period was based on data from 2016-19 and the pandemic period was based on data from 2020. This was calculated using the life table method.

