**Life tables**

We will report the lifetime risk of surgery using life tables, this is considered a more accurate method for lifetime risk in comparison with cumulative risk as it considers the competing risk of death in the population(11). This will be calculated with a 95% confidence interval. The lifetables method has been used to calculate the lifetime risk of diabetes(9, 10). To calculate lifetime risk via the lifetable method we need to find the incident rate, mortality rate of those that have had surgery and the mortality rate for those who have not had surgery in each 5-year epoch. This can be done using the following equations(9):

[figure not shown]

[figure not shown]

Where
[figure not shown]
 is all-cause mortality,
[figure not shown]
 is the age-specific morality rate for those who have had surgery,
[figure not shown]
 is the age-specific morality rates for those that have not had surgery, Relative risk (RR) is the age-specific relative risk of mortality for those who have had surgery and
[figure not shown]
 is the age-specific prevalence of surgery.

The incident and mortality rates can then be used to find out the probability that a patient will transition from the state of not having surgery to having surgery or death and from having surgery to death, this is shown in the following equations(9):

Probability of transitioning from no surgery to death:

[figure not shown]

Probability of transitioning from no surgery to surgery:

[figure not shown]

Probability of transitioning from surgery to death:

[figure not shown]

Where IR is the age-specific incident rate of surgery and L is a period of time (five years). This will allow us to calculate the probability that a person aged x who has not had surgery will have surgery before reaching age x+1 or will die without having surgery before reaching age x+1. This can be applied to a hypothetical cohort to estimate the number of individuals in the population undergoing surgery at each 5-year epoch.

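### Equation 1 uses m_i − s_i as the death rate of people without surgery, which in general it is not; s_i is undefined and the assumption behind the term is neither stated nor tested

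*SAP*

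**What the plan says.** The SAP's Statistical Analysis section makes the life table the primary method. The Change log, dated 22 December 2023, amended it, and Appendix 2 (The Life Table Method) repeats the amended equations.

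- Equation 1 sets the exit hazard as "\lambda_{i}=r_{i}+m_{i}-s_{i}", where "m_{i}$ is the all-cause mortality rate and $s_{i}$ is the surgical mortality rate".
- On how the rates are obtained there is only this: "We calculated surgical mortality rate and the all-cause mortality rate in person-years for each 5-year epoch".
- Equation 2 turns the hazard into a survival function: "The probability of being alive and without previous surgery at age i was calculated using equation 2".

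No time window, cause rule or denominator population is given for s_i. The only death outcome listed, under Outcomes, is death in patients who have had surgery, also without a window.

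The Life tables section, written before the amendment, asked for the "mortality rate of those that have had surgery and the mortality rate for those who have not had surgery", linked through prevalence and the "age-specific relative risk of mortality for those who have had surgery". Sample table 1 still carries the column "Mortality rate for those who have not undergone surgery". The SAP gives no value for the relative risk, incidence, mortality, prevalence or lifetime risk.

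**The concern.** S_0 follows people who are alive and have never had surgery, so the death part of its hazard must be the death rate of those people. Equation 1 supplies all-cause mortality less a surgical component. Whether that equals the required rate depends on what s_i counts and on how mortality differs between operated and unoperated people.

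For a rare event the difference would hardly matter. Prior surgery is common, and most common at the ages when most deaths occur, so the two rates can differ materially there. The primary lifetime risk is affected. The error is structural, so the planned 95% confidence interval would not reveal it however many records are used.

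**Working it through.** **Algebra.** Let p be the share of survivors already operated on, m0 the death rate without surgery and m1 the death rate after surgery. Then m = (1−p)·m0 + p·m1.

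- *Reading A: s is surgery-caused deaths per whole-population person-year.* Write n1 for the non-surgical death rate of operated people, so p·m1 = s + p·n1. Then m − s = (1−p)·m0 + p·n1. This equals m0 only if n1 = m0. If n1 is higher, the term is too large, S_0 too small and lifetime risk too low.
- *Reading B: s is all deaths in operated people per whole-population person-year.* Then s = p·m1 and m − s = (1−p)·m0. The term is too small and lifetime risk too high.
- *Target.* With m1 = RR·m0, m0 = m/(1 + p(RR−1)). These are the quantities that the Life tables section names.

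**Inputs.** The SAP has no figure to reproduce, so all of these are assumptions except where noted.

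- 19 five-year bands from 0–4 to 90–94; m = 0.00003·exp(0.098·age) + 0.0002 at mid-band (life expectancy about 76).
- Yearly hazard of first surgery among the surgery-free: base 0.3% at birth rising to 2.5% at age 80; flat 1%; steep 0.5% rising to 4%.
- RR 1.5, 2 and 3, constant over age and lasting for life.
- s/m = 9%, range 0 to 15%. The 9% comes from the SAP Background: 5.1 million × 1% = 51,000 deaths, over an assumed 550,000 deaths a year.
- Survival taken to the start of each band; p generated by the cohort itself.

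**One band (80–84, base, RR 2).** m = 0.00003·exp(0.098 × 82.5) + 0.0002 = 0.0976 and p is about 0.56. The target is 0.0976/(1 + 0.56) = 0.0626. Reading A at 9% gives 0.91 × 0.0976 = 0.0888, which is 1.42 times the target (1.33 to 1.56 times for s/m from 15% to 0). Reading B gives 0.44 × 0.0626 = 0.0275.

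**Lifetime risk, reading A, base, s/m = 9%.** Equation 1 gives 63.9%.

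- RR 1.5: target 64.9%, gap −1.0 points
- RR 2: target 66.1%, gap −2.2 points
- RR 3: target 67.8%, gap −3.9 points

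**Gaps in points, equation 1 minus target.** The first three columns are reading A, each cell for s/m = 0 / 9% / 15%.

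| Hazard | RR 1.5 | RR 2 | RR 3 | Reading B, RR 1.5 / 2 / 3 |
|---|---|---|---|---|
| Flat | −0.9 / −0.4 / −0.1 | −1.5 / −1.1 / −0.8 | −2.4 / −1.9 / −1.6 | +2.4 / +2.0 / +1.5 |
| Base | −1.8 / −1.0 / −0.4 | −3.0 / −2.2 / −1.7 | −4.7 / −3.9 / −3.4 | +5.0 / +4.3 / +3.4 |
| Steep | −2.0 / −1.2 / −0.7 | −3.3 / −2.6 / −2.1 | −5.1 / −4.4 / −3.9 | +5.9 / +5.0 / +3.8 |

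**Where the gap vanishes.** In the base case at s/m = 9% it is nil at RR 1.2 (63.9% both ways). It also vanishes at s/m of about 20%, 30% and 45% for RR 1.5, 2 and 3, and is positive above those values.

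**Second model.** With three other mortality curves and incidence scaled to a lifetime risk of 50 to 80%, reading A with s = 0 gave gaps of −0.8 to −2.6 points at RR 1.5 and −2.0 to −7.0 at RR 3. In the central mortality set, with s at 1% of operations, they were −0.4 to −1.3 and −1.8 to −5.2. Reading B again reversed the sign.

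**The case against.** Four arguments stand against a stronger claim.

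- *Direction and size.* A reader might infer that the primary result is biased downwards by 1 to 4 points. The documents do not support that. The sign turns on the meaning of s_i, which the SAP leaves open, and the listed death outcome is at least compatible with reading B. The size turns on RR values that the SAP never gives, and a relative risk of 2 or 3 lasting for life after any operation, including one in childhood, has no basis in it.
- *Superseded text.* The Life tables section and Sample table 1 predate the amendment, so their difference from Appendix 2 does not show that equation 1 is wrong. This stands. The point rests on equations 1 and 2, both current; the older text shows only that the needed rate had once been specified.
- *Choice of method.* A reader might infer that the relative-risk formula must replace equation 1. Records start in April 2015, so people without surgery in the window include many operated on earlier. An RR estimated there does not compare ever-operated with never-operated people, and making it the headline would exchange one assumption for another.
- *Scope.* The calculation covers first surgery. Supplementary figure 3 also applies the life table to all surgery, which it does not address.

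None of this makes m_i − s_i equal to the no-surgery death rate, supplies a definition of s_i, or states the assumption.

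**Conclusion.** The point holds in a form that is neutral on direction. The death term in equation 1 is the hazard that equation 2 needs only under an assumption of equal non-surgical mortality, and only if s_i means surgery-caused deaths per whole-population person-year. The SAP fixes neither and plans no check of either.

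For first surgery, with surgery-free incidence denominators, RR 1.5 to 3 and s/m 0 to 15%, lifetime risk is too low by about 0.1 to 5 points across the three hazard shapes. The second model's curves reach 7 points at RR 3 with s = 0. Under the other meaning of s_i it is too high by about 1.5 to 6 points. These figures show what could be at stake; they do not estimate the error in this study. The matter should be settled because it touches the primary result and can exceed what a confidence interval from national data would show.

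**What to change.** - Define s_i in Appendix 2: the cause rule or time window after surgery, and a whole-population person-year denominator.
- State beside equation 1 that m_i − s_i assumes equal non-surgical mortality in operated and unoperated people.
- For first surgery, pre-specify a sensitivity analysis with λ_i = r_i + m_i/(1 + p_i(RR_i − 1)), taking p_i band by band from the life table and RR = 1, 1.5, 2 and 3. Report it beside the primary lifetime risk. The RR = 1 run uses m_i in full, so it will not reproduce equation 1 unless s_i is zero.
- Label any RR estimated from the records from April 2015 as within-window, not ever versus never operated. It need not replace the primary equation.
- Bring Sample table 1 into line with whichever death rates are used.

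The cost is a few lines of SAP text and a few extra life-table runs, with no new data. The downside is a headline figure shown with a range.

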***Statistical Analysis***

There are two validated methods to measure lifetime risk – life tables and cumulative risk. We will calculate the lifetime risk of surgery using both methods, with life table’s being the primary method.

We will report the total number of patients undergoing surgery, as defined using the OPCS-4 codes, in the time frame assessed. This data will be categorised by 5-year epochs. We will then divide the total number of patients undergoing surgery for each 5-year epoch by the total population in that 5-year epoch using population estimates from ONS data. This will give us the age-specific incidence rates of surgery per head of the population.

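### Equations 2–4 of the primary life-table method are mis-indexed and contradict one another; equation 6 has the same summand error

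*SAP*

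**What the plan says.** The SAP calculates lifetime risk by two methods, with life tables "being the primary method" (Statistical Analysis). On the bands it says "The number of patients undergoing surgery will be categorised into 5-year age epochs e.g. Age 0-4, 5-9, 10-14", running to 90+ (Derivation of variables). That makes 19 bands.

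The current life-table equations stand in Appendix 2, The Life Table Method, and identically in the change log entry of 22 December 2023:

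- Equation 1 gives the rate of leaving the alive and surgery-free state: λ_i = r_i + m_i − s_i (incidence of surgery, plus all-cause mortality, minus surgical mortality).
- Equation 2 is introduced by "The probability of being alive and without previous surgery at age i was calculated using equation 2" and printed as "S_{0}(i)=exp[-5\sum_{x=5}^{i} \lambda_{i" (closing bracket cut here). The factor is explained by "This was multiplied by 5 due to 5-year epochs being used".
- Equation 3 gives the contribution of band i: l_i = S0(i) × r_i × [1 − exp(−5λ_i)]/λ_i.
- Equation 4 adds l_i from i = 0 to 90.
- Equation 6, for cumulative incidence until age i, is P = 1 − exp(−5 Σ r_i), again with x running from 5 to i.

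**The concern.** Equation 3 needs the probability of entering band i alive and surgery-free; its last factor then deals with losses inside the band. Equation 2 should therefore cover only the bands already passed. As printed, it starts at x = 5, runs up to i itself, and has a summand that does not depend on x. Equation 4, by contrast, starts at i = 0.

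This is the primary method for the only primary objective. The captions of Supplementary figures 3 and 4, which compare pre-pandemic with pandemic risk, also name the life-table method. A programmer who followed the text could obtain materially different lifetime risks, or even a value above 100%.

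**Working it through.** **Inputs.** The bands and equations are those listed above. The SAP gives no values for r, m or s (the sample tables are empty shells) and no lifetime risk, so there is no figure to reproduce. All rates below are assumptions, per person-year.

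**1. Lower-age labels (i = 0 is 0–4, as equation 4 requires).** Take i = 10. Someone reaching age 10 has passed bands 0–4 and 5–9, so the sum needed is λ_0 + λ_5. Equation 2, with summand λ_x, gives λ_5 + λ_10. It leaves out 0–4 and removes the losses of 10–14 before that band begins. Equation 3 then removes them again.

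**2. Upper-age labels (x = 5 is 0–4).** Equation 2 at i = 10 now covers 0–4 and 5–9, which is right for survival to age 10. But λ_10 and r_10 in equation 3 then belong to 5–9, a band already finished. Each contribution is multiplied by exp(−5λ_i). In equation 4 the i = 0 term has no band, and the 90+ band has no term.

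**3. The summand as printed.** The sum has i/5 identical terms, so S0(i) = exp[−5 × (i/5) × λ_i] = exp(−iλ_i). This depends on one band's rate only.

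**4. Size of the shift under lower-age labels with λ_x.** Consistent exponent: −5(λ_0 + … + λ_(i−5)). Equation 2 exponent: −5(λ_5 + … + λ_i). The ratio of contributions is exp[−5(λ_i − λ_0)]. At i = 0 the sum is empty and the ratio is 1.

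**5. Checks without mortality (λ = r).**
- r rising linearly from 0.01 to 0.05: Σr = 19 × 0.03 = 0.57, so the answer must be 1 − exp(−2.85) = 94.2%. The consistent version returns 94.2%; the shifted version returns 86.9%.
- r flat at 0.02: 1 − exp(−5 × 19 × 0.02) = 85.0%, and all versions agree.
- r = 0.10 at 0–4, then 0.02: the correct value is 1 − exp[−5(0.10 + 18 × 0.02)] = 1 − exp(−2.3) = 90.0%. Equation 2 gives 1 − exp(−0.5) = 0.3935 for the first band. The other 18 bands add exp(−0.1) − exp(−1.9) = 0.9048 − 0.1496 = 0.7553. The total is 1.149, or 114.9%. The literal summand gives the same value here, because the rate is constant from age 5.

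**6. With mortality.** Assumed: m between 0.0001 and 0.22 (0.001 at 0–4, highest at 90+) and s = 10% of m.

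| Assumed r by age | Consistent | Equation 2 with λ_x | Equation 2 literal |
|---|---|---|---|
| flat 0.01 | 54.8% | 53.3% | 46.5% |
| flat 0.02 | 79.0% | 77.6% | 70.9% |
| rising 0.005 to 0.03 | 70.3% | 64.1% | 45.5% |
| rising 0.01 to 0.05 | 86.6% | 78.8% | 58.2% |
| rising 0.02 to 0.15 | 98.3% | 84.9% | 64.7% |
| humped, 0.01 to 0.03 | 82.5% | 84.0% | 75.8% |
| falling 0.04 to 0.01 | 88.0% | 90.2% | 94.4% |
| falling 0.06 to 0.01 | 94.8% | 98.4% | 107.1% |

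From unrounded values, the shift moves the total by between −13.5 points (98.34 to 84.87) and +3.6 points (94.80 to 98.42). The literal summand moves it further in all eight rows.

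**7. Equation 6.** With r_x and upper-age labels, x = 5 to i covers exactly the years up to age i. With lower-age labels it drops 0–4 and adds the band that begins at i. For the humped rates at i = 90, that gives 85.0% against 86.5% to exact age 90; with a flat rate the two agree. The printed r_i, taken literally, reduces the formula to 1 − exp(−i r_i).

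**The case against.** The best defence is that this is a labelling slip. The sum from x = 5 to i in steps of five has i/5 terms, which times 5 is exactly i years. If x in equation 2 is an upper age, i in equations 3 and 4 is a lower age, and the summand is read as λ_x, the system is correct. That may well be what was intended, but it needs two labelling conventions and a silent change of index, none of which the SAP states. No single convention makes equations 2 to 4 agree. For equation 6 the defence succeeds as far as the limits go: it stands alone, and upper-age labels make them right. Only its summand is wrong on every reading.

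A reader might infer that every primary lifetime-risk figure is wrong. The SAP does not support that: it contains no results and no code, and a misprinted index does not show what the program did. Even on the shifted reading, the 0–4 contribution is right, as is that of any band with λ_i = λ_0. Nor can one say that older ages are always under-weighted, since the sign follows λ_i − λ_0 and the SAP gives no rates. A claim that the error exceeds the confidence intervals also fails, because none are reported.

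**Conclusion.** The point holds as a fault in the printed formulas of the primary method. Equations 2 to 4 cannot all be right under one band labelling, and the summand in equations 2 and 6 carries the wrong index. This is more than missing detail: followed as printed, the equations can return a lifetime risk above 100%.

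The multiplier exp[−5(λ_i − λ_0)] is exact for lower-age labels with λ_x. The range of about −13.5 to +3.6 percentage points rests wholly on the assumed rates, and the effect is nil under a flat hazard. Whether any computed result is affected cannot be told from the SAP.

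**What to change.** - State that i and x denote the lower ages of bands.
- Replace equation 2 by S0(0) = 1 and S0(i) = exp[−5 Σ λ_x], with x = 0, 5, …, i−5. Equations 3 and 4 can then stand.
- In equation 6 use r_x, and set the limits under the same labelling so that they cover every band from 0–4 up to the stated age.
- Make the same corrections wherever the life-table equations are repeated in the change log.
- Add a program check that surgery, death without surgery, and still alive and surgery-free sum to 1.
- Confirm which formulas the analysis code used. Re-run the lifetime-risk results only if it followed the printed ones.

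The cost is a few corrected lines, one check and a look at the code. Any re-run uses the same inputs and needs no new data.
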